#### Secondary endpoints

The following secondary endpoints will be recorded:
Static lung compliance (ml/cmH_2_O) (measured at least once daily at 8:00 a.m. during the first 7 days)Duration of mechanical ventilation (h) from ICU admission to first extubation success (> 48 h without reintubation)Length of ICU stay (h)Length of stay in the hospital (days)Incidence of multi-organ failure (a SOFA score of 3 or more in at least two organ systems [49]), assessed daily during the first 7 daysIncidence of VAP according to both the American Thoracic Society (ATS) [50] and the Center for Disease Control and Prevention (CDC) [51] definitions, assessed daily during the first 7 daysMortality on day 30

The effects of dornase alfa and normal saline will be assessed according to the plasma concentrations of DAMPs (mitochondrial DNA, HMGB-1, HSP70, sRAGE) and NETs (Strasbourg centre only) divided into quartiles at day 0, day 3 and day 5. It is anticipated that trauma patients with the highest blood concentrations of either DAMPs or NETs will develop the most severe complications (including hypoxaemia and ARDS). The time course of DAMP and NET blood concentrations will also be analysed according to treatment group to unveil a potential quicker decrease in patients randomized in the dornase alfa group.

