#### Secondary objectives

The secondary objectives are to demonstrate, using aerosolized dornase alfa as compared to placebo, an improvement in static lung compliance, a reduction in mechanical ventilation duration or an increase in ventilation-free ICU days, a reduction in the length of ICU stay, a reduction in the hospital length of stay, a reduction in the incidence of multi-organ failure, a reduction in the incidence of ventilator-associated pneumonia (VAP) and a reduction in mortality at day 30.

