### Trial design {8}

This will be an investigator-initiated, institution-led, multicentre, double-blinded, placebo-controlled, parallel-group, superiority, randomized trial in ventilated, trauma ICU patients.

Randomization will be carried out through a secure web-based randomization system, stratified by the centre and the presence of severe traumatic brain injury (Glasgow Coma Score < 9 on scene).

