### Relevant concomitant care permitted or prohibited during the trial {11d}

#### Standardization of respiratory care

Daily care for the included patients will be protocolized according to good clinical practices, especially concerning respiratory care (semi-recumbent position, protective mechanical ventilation (6–8 ml/kg predicted body weight), PEEP > 5 cmH_2_O, plateau pressure < 30 cmH_2_O, close tracheal cuff pressure monitoring, early enteral feeding (500 ml on day 1), glucose control and protocolized sedation based on both CPOT and RASS scores [46]). Adherence to guidelines will be checked in every centre for every patient.

Patients will be followed until day 30 for the record of study outcomes.

Every concomitant care will be allowed except aerosols during study drug administration.

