The aim of this study is to show that the frequency of moderate-to-severe hypoxaemia is lower in the dornase alpha group than in the placebo group. The main variable is then dichotomous “moderate-to-severe hypoxaemia yes/no”, modelled in a logistic mixed regression. We will assume that this variable is Bernoulli distributed with parameter π. The logit of this parameter (linear predictor) is additively written as:
$$ \mathrm{logit}\left({\pi}_i\right)={\alpha}_0+{\alpha}_1I\left({g}_i=1\right)+{\beta}_i, $$

where:
*α*_0_ is a grand mean, with mean 0 normal prior (the variance in this normal is 6, corresponding to a low informative prior)*I*(*g*_*i*_ = 1) is a dummy covariate coded for the group of subject *i* (1 for the dornase alpha group and 0 for the placebo group) — the prior on the parameter of this covariate is the same normal as that for the grand mean*β*_*i*_ is a (random) subject effect, on which is assumed a normal prior with mean 0 and low variance (e.g. 10)

Because the linear predictor is on the logit scale, the probability for moderate-to-severe hypoxaemia will be obtained by monitoring the back-transformation of the logit.

This regression model without covariates except group will be completed for taking into account potential confounding variables. In the model, the entire set of these variables will be added and, secondly, selected using stochastic search variable selection (SSVS) [53]. In such a model, the prior distribution on each parameter is a mixture of two mean 0 normal distributions, one with low variance and the other with high variance: if the posterior weight on this second normal is strongly around 0, then the prior on the parameter is essentially driven by a normal distribution whose mean is centred on 0; this is the clue for a “non-significant” parameter.

The secondary analyses will be conducted as the main analysis with a regressive model, testing the difference of a parameter between the two groups. Only the likelihood model will be changed to take into account the type of variable studied: γ distribution for continuous variables such as length of stay and duration of ventilation. Dichotomous variables such as 30-day mortality will be studied with logistic regression.

No statistical procedure for replacing missing values will be used. All variables and subjects will be considered in the descriptive analyses, but, for inference, 20% missing data or more will result in rejection of the variable or individual.

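### Ventilation time stops only at a successful extubation, so a survivor weaned with a tracheostomy in place has no valid end time on this secondary endpoint (minor)

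*Protocol article*

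**What the plan says.** Under Outcomes {12}, Secondary endpoints, the article gives ventilation time one start, one stop and one success criterion: "Duration of mechanical ventilation (h) from ICU admission to first extubation success (> 48 h without reintubation". The Secondary objectives section states the aim more loosely, as "a reduction in mechanical ventilation duration or an increase in ventilation-free ICU days". Ventilation-free days do not reappear in the endpoint list and are not defined.

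On the population, Eligibility criteria {10} asks for an ISS above 15 and ventilation expected to last more than 48 h. Trial design {8} has randomisation "stratified by the centre and the presence of severe traumatic brain injury".

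On follow-up and analysis:
- The section on respiratory care says "Patients will be followed until day 30 for the record of study outcomes". Table 1 schedules visits on days 1 to 7 and a close-out at day 30.
- Statistical methods {20a} assigns a "γ distribution for continuous variables such as length of stay and duration of ventilation" and mentions no censoring.
- The same section says "No statistical procedure for replacing missing values will be used" and adds that "for inference, 20% missing data or more will result in rejection of the variable or individual".

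Tracheostomy, decannulation and disconnection from the ventilator with an airway still in place are mentioned nowhere in the article.

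**The concern.** The endpoint is named for time on the ventilator but is timed by removal of a tube. For a patient who is extubated and stays extubated, the two coincide. For a patient who receives a tracheostomy and then breathes unaided through it, they do not: the stop event either never occurs or occurs at a moment unrelated to ventilator support.

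It is reasonable to expect some such patients among severely injured adults who are ventilated for days and include a severe brain injury stratum, although the article does not say so. At stake is how well one named secondary objective is measured. If the end time is left empty, surviving and successfully weaned patients leave the analysis. If another date is substituted, their ventilation time is too short or too long.

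**Working it through.** The article states no figure on this point, so there is nothing to reproduce. The check applies the rule as written and then shows, under labelled assumptions, how large the effect could be.

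**Applying the rule.** Take a hypothetical survivor with a tracheostomy on day 8 who is off the ventilator for good from day 12. Ventilation time is 12 days.

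- No extubation recorded: the end time is empty.
- Tube exchange counted as extubation: 8 days, which is 4 days short, with the patient still ventilated.
- Decannulation counted as extubation: the recorded time exceeds 12 days by however long the cannula stays in. If it is still in at day 30, the end is not observed and the value is again empty.

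**Does anything else in the article repair this?** The alternative measure, ventilation-free days, is undefined. The gamma model has no stated way to use an incomplete time. Missing values are not replaced. An empty end time therefore removes the patient from this analysis.

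**How many patients.** Input from Sample size {14}: 250 per arm. Assumed tracheostomy share t: 5%, 10%, 20%. Then 250 × t = 12.5, 25 and 50 per arm.

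**Illustrative effect on an arm mean.** Assumed means, none from the article: 8 days of ventilation without tracheostomy and 20 days with it. Assumed delay from end of ventilation to decannulation: D = 5 or 10 days. A longer delay would put the average decannulation beyond day 30 (20 + 10 = 30), where it would not be observed.

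- True mean = (1 − t) × 8 + t × 20
- Mean if these patients are dropped = 8
- Mean if decannulation is used = true mean + t × D

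| t | True mean (days) | Error if dropped | Error if decannulation used, D = 5 to 10 |
|---|---|---|---|
| 5% | 8.6 | 8/8.6 − 1 = −7% | 0.25/8.6 to 0.5/8.6 = +3% to +6% |
| 10% | 9.2 | 8/9.2 − 1 = −13% | 0.5/9.2 to 1.0/9.2 = +5% to +11% |
| 20% | 10.4 | 8/10.4 − 1 = −23% | 1.0/10.4 to 2.0/10.4 = +10% to +19% |

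These are errors in an arm mean. If both arms have the same tracheostomy share, timing and handling, they largely cancel in the comparison.

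**When the comparison itself moves.** Suppose the shares were 20% on placebo and 15% on dornase alfa. The true difference from that source is 0.05 × (20 − 8) = 0.6 days. With these patients dropped it is 0. With decannulation 10 days later it is 0.05 × (30 − 8) = 1.1 days. This requires treatment to change the tracheostomy rate, for which the article offers no evidence.

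**The 20% missing-data rule.** It would be reached through this route alone only if the share were at least 20% and every such end time were left empty.

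**The case against.** The strongest reply is that this is one line in a journal article. The full protocol (version 8.0) is posted on a registry and is not shown here, and a coding rule for tracheostomised patients could sit there, in the eCRF guide or in the analysis plan. The endpoint's name also declares ventilator time as the quantity of interest, so a sensible site might simply enter the time off the ventilator. It would therefore go too far to say that sites have no choice but a wrong date. What survives is that the article does not merely stay silent: it fixes a stop event, and a site that follows the wording exactly does not record ventilator time for these patients.

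Several stronger readings are tempting and are not supported:

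- *Recorded durations above 30 days.* Outcomes are recorded to day 30. The six-month contact described under post-trial care covers a dyspnoea questionnaire and a chest X-ray, not airway status. A later decannulation would be unobserved rather than entered as a long value.
- *Bias between the arms.* Airway practice may well differ by centre and by brain injury, but these are the two randomisation strata, and care providers and outcome assessors are blinded. Such differences should be roughly balanced.
- *The longest-ventilated patients are the ones mis-measured, exactly where benefit would show.* This is a plausible clinical inference, but the article gives no ventilation times or tracheostomy rate to support it.

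**Conclusion.** The point holds as a minor one. The stated stop event does not measure time on the ventilator for survivors weaned with a tracheostomy in place, and nothing elsewhere in the article corrects it. The expected harm is measurement error and selective loss of patients in a single secondary endpoint.

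The size is not established. The count of about 12 to 50 per arm rests on an assumed 5% to 20% share, and the percentage errors rest further on assumed durations and delays. A reader might infer that the trial's main conclusion is at risk. It is not: the primary endpoint is hypoxaemia in the first 7 ICU days, and neither it nor the sample size depends on this definition.

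**What to change.** Replace the stop event with wording such as: ventilation ends at the start of the first period of more than 48 h without invasive ventilatory support, whether reached by extubation or by disconnection from the ventilator with a tracheostomy in place. If ventilation-free ICU days are reported, derive them from the same rule. This changes how an outcome is recorded and leaves patient care as it is.

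The cost is one sentence in the endpoint definition and one eCRF field for the date and time off the ventilator. The field must stay open to day 30, because Table 1 schedules daily visits only to day 7 and many of these dates would fall later. Recruitment began in March 2019, so for patients enrolled before the change the date would have to be taken from their ICU records.

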#### Ancillary mechanistic study

On days 0, 3 and 5, additional blood samples (6 ml on each day) will be drawn into EDTA tubes, centrifuged and stored (− 80 °C) for subsequent analysis of DAMPs (mitochondrial DNA by qPCR; HMGB1, HSP70 and sRAGE by ELISA) at the end of enrolment. Whole blood samples will be drawn (days 0, 3 and 5) for extemporaneous quantification of NETs on fresh blood using a flow cytometric assay [45] in patients at the Strasbourg centre.

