### Sample size {14}

The sample size was determined to be 250 subjects per arm (i.e. 500 subjects in total). Dornase alfa is expected to reduce the incidence of moderate-to-severe hypoxaemia from 0.45 to 0.30. Considering a reasonable standard deviation of 0.03, and using Bayesian techniques [52], 200 subjects per arm were estimated to show a difference of more than 0.12 (instead of the expected 0.15). Assuming 25% loss to follow-up, this number was increased to 250 subjects per arm, although these subjects will not be replaced.

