### Recruitment {15}

Patients will be recruited in seven French participating hospitals, both university-affiliated and non-university-affiliated and admitting severe trauma patients:
Hôpitaux Universitaires de Strasbourg, Hôpital de Hautepierre (150 severe trauma patients per year)Hôpitaux de Colmar, Hôpital Louis Pasteur (50 severe trauma patients per year)Centre Hospitalo-Universitaire de Reims, Hôpital Maison Blanche (150 severe trauma patients per year)Centre Hospitalier Régional Metz-Thionville, Hôpital de Mercy (50 severe trauma patients per year)Groupe Hospitalier de la Région de Mulhouse et Sud-Alsace, Hôpital du Moenchsberg—Emile Muller (50 severe trauma patients per year)Centre Hospitalier Régional Universitaire de Nancy, Hôpital Central (220 severe trauma patients per year)Assistance Publique—Hôpitaux de Paris, Hôpital Universitaire Pitié Salpêtrière—Charles Foix (500 severe trauma patients per year)

Taken as a whole, more than 3500 patients per year fulfil the inclusion criteria, allowing for an inclusion ratio of one patient included out of seven patients admitted to one of the participating centres.

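### Cutting continuous DAMP and NET concentrations into quartiles loses some power in an ancillary analysis and leaves NET cells too small to estimate an effect

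*Protocol article*

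**What the plan says.** Under Secondary endpoints, after the list of clinical endpoints, the protocol article states: "The effects of dornase alfa and normal saline will be assessed according to the plasma concentrations of DAMPs". The DAMPs are mitochondrial DNA, HMGB-1, HSP70 and sRAGE. The sentence goes on to "NETs (Strasbourg centre only) divided into quartiles at day 0, day 3 and day 5". The next sentence gives the expectation: "It is anticipated that trauma patients with the highest blood concentrations of either DAMPs or NETs will develop the most severe complications". A third plans a comparison of the time course of the concentrations between arms and does not mention quartiles.

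The Ancillary mechanistic study section describes the assays: "mitochondrial DNA by qPCR; HMGB1, HSP70 and sRAGE by ELISA" for the DAMPs, and "extemporaneous quantification of NETs on fresh blood using a flow cytometric assay" for NETs, at Strasbourg only. Table 1 places study treatment on days 0 and 1 and blood sampling on days 0, 3 and 5.

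The article does not say how quartiles would enter a model. It names no interaction test, contrast or trend, and gives no subgroup size or power for this analysis.

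**The concern.** qPCR, ELISA and flow cytometry all give values on a continuous scale. Quartile boundaries taken from the sample have no biological meaning and will move with the case mix. Within a quartile, all patients are treated as having the same marker level.

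What is at stake is the chance of seeing whether the treatment effect varies with DAMP or NET load. Grouping weakens that comparison, and a four-way split of each arm invites separate estimates within quartiles. For NETs, measured at one of seven centres, those cells could be very small. The regression already planned under Statistical methods {20a} accepts a continuous covariate, so the loss is avoidable.

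**Working it through.** The article gives no figure of its own for this analysis, so there is none to reproduce.

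**Inputs from the article.** Sample size: "The sample size was determined to be 250 subjects per arm (i.e. 500 subjects in total". Event rates: "Dornase alfa is expected to reduce the incidence of moderate-to-severe hypoxaemia from 0.45 to 0.30". Loss to follow-up: 25%. Strasbourg volume: "Hôpital de Hautepierre (150 severe trauma patients per year". The seven listed volumes sum to 150 + 50 + 150 + 50 + 50 + 220 + 500 = 1,170 per year.

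**Assumptions.** Log concentration is normally distributed and the relation is linear on that scale. A two-sided 5% test stands in for the Bayesian analysis, for which no decision rule is given here.

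**Information kept by quartiles.** The quartile means of a standard normal variable are ±0.325 and ±1.271. The share of variance between quartiles is (2 × 1.271² + 2 × 0.325²)/4 = 0.861. With quartiles scored 1 to 4, the squared correlation with the marker is 0.856. About 14% is lost either way.

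**Power.** If the continuous term has power P, its noncentrality is λ = (1.96 + z_P)². Unordered quartiles have 0.861λ on 3 degrees of freedom; the trend score has 0.856λ on 1. At P = 80%, λ = 7.85, which becomes 6.76 on 3 df (57.3%) or 6.72 on 1 df (73.6%).

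| Continuous | Unordered (3 df) | Loss, points | Trend (1 df) | Loss, points |
|---|---|---|---|---|
| 20% | 12.1% | 8 | 17.9% | 2 |
| 30% | 17.4% | 12.6 | 26.4% | 3.6 |
| 50% | 30.0% | 20.0 | 44.2% | 5.8 |
| 70% | 46.5% | 23.5 | 63.3% | 6.7 |
| 80% | 57.3% | 22.7 | 73.6% | 6.4 |
| 90% | 71.4% | 18.6 | 85.1% | 4.9 |
| 95% | 81.1% | 13.9 | 91.6% | 3.4 |

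**Simulation check.** Model: logit(p) = −0.2 − 0.65g + 0.5x + b·x·g, which gives risks of about 45% and 30% at the mean marker value x = 0. There were 1,000 runs per setting at N = 500, with likelihood-ratio tests. Power for continuous, unordered and trend was 52%, 30% and 47% at b = −0.4; 86%, 67% and 81% at b = −0.6; and 96%, 81% and 92% at b = −0.7. This agrees with the table. The slopes are assumed; the article states none.

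**NET cell size.** If enrolment follows listed volume, 500 × 150/1,170 = 64 patients, and 64/(2 arms × 4 quartiles) = 8 per arm per quartile. Other assumptions give:
- 25% loss: 375 × 150/1,170 = 48 patients, 6 per cell
- equal shares across seven centres: 500/7 = 71 patients, about 9 per cell
- Strasbourg enrolling 25%: 125 patients, about 16 per cell

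**What such a cell can show.** At 45% against 30%, the approximate 95% half-width for the risk difference with 8 per arm is 1.96 × √[(0.45 × 0.55 + 0.30 × 0.70)/8] = 0.47, or 47 points. With 6 per arm it is 54 points and with 16 it is 33. A two-sided Fisher exact test rejects 4.0% of the time with 8 per arm, 1.1% with 6 and 6.9% with 16.

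**DAMP cell size.** With 400 evaluable patients (the 200 per arm before inflation for loss), a quartile holds 50 per arm. The half-width is 1.96 × √(0.4575/50) = 0.19, or 19 points, against an expected difference of 15.

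**If the effect sits only in the top quartile.** Where the linear term has 80% power, the 3-df quartile test has 91%. The ranking reverses.

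**The case against.** Four objections carry weight.

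First, the larger loss depends on an unordered 3-df test that the article never names. How quartiles enter the model can properly be left to the full protocol or analysis plan. With a trend score the loss is 3 to 7 points. This stands, so the upper figure is a ceiling and not a description of the plan.

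Second, a reader might infer that the plan expects the benefit of dornase alfa to rise with marker level, and that quartiles undercut its own dose-response hypothesis. The text does not support that. The stated expectation links high concentrations to worse complications, which is a prognostic statement. It speaks of the highest concentrations, so a threshold is as compatible with it as a straight line, and under a threshold quartiles can do better.

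Third, a reader might take this to be the trial's only mechanistic test. It is not: the time-course comparison by arm is a separate mechanistic analysis, compares randomised groups and involves no quartiles.

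Fourth, NET numbers are small because the assay needs fresh blood at one centre, not because of quartiles. With 64 patients the continuous interaction is also weak: simulated power is 29% against 20% for unordered quartiles at b = −0.7, and 59% against 42% with a main slope of 0.8 and b = −1.2. The change helps but does not rescue the NET analysis.

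None of this gives a reason to prefer quartiles for inference. The article fixes the cut, cites no basis for it, and a better use of the same samples is available.

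**Conclusion.** The point holds as a minor one. For a normal marker and a linear relation on the log scale, quartiles discard about 14% of the information. Interaction power falls by about 3 to 7 points with a trend score and by about 13 to 24 with unordered categories, when the continuous analysis would have between 30% and 95% power. The loss is smaller below that range.

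The figure of 8 patients per arm per NET quartile requires enrolment in proportion to listed centre volume, which the article does not state. Across the 6 to 16 range the conclusion is the same: within-quartile NET effects cannot usefully be estimated.

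The analysis is ancillary. Neither the primary comparison nor the time-course analysis is affected.

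**What to change.** Under Secondary endpoints, make the inferential analysis a model with group, day-0 log concentration as a continuous covariate, and their product. For the hypoxaemia endpoint this is the planned logistic regression with two added terms. Report the posterior of the interaction and the treatment effect as a curve over concentration. For the DAMPs, add a restricted cubic spline to detect a threshold shape. For NETs, use the linear term only. Keep quartiles as a descriptive display.

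State openly that day 3 and day 5 values follow treatment on days 0 and 1. Groups formed on them are post-randomisation groups whether or not the marker is cut, so they should not serve as effect modifiers and should stay in the time-course analysis. This removes two of the three time points from the effect-by-marker analysis and should be declared as a change. State also that the day-0 sample precedes the first dose; the article does not say so, and the model relies on it.

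The cost is a few sentences and slightly different model code, with no extra patients, samples or assays. The downside is that a linear term is less sensitive when the effect is confined to the top quartile. The DAMP spline and the quartile display are there to show that; for NETs only the display can.
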